#### Follow-up analyses

To measure the long-term effects of the SHAPE intervention, secondary analyses will be conducted for all participants who received the intervention (i.e. including post-waitlist participants going on to receive SHAPE). Secondary outcome measures for these analyses will include dichotomous SCID-5 diagnosed PTSD and MDD at 6 months post-intervention completion, and continuous symptom, resilience, and wellbeing measures collected at 6 months post-intervention completion.

To test if there is a significant difference between receiving SHAPE immediately or after waitlist, between-group analyses of the dichotomous and continuous secondary outcome measures at 6 months post-intervention completion will first be conducted. If there are no significant group differences, within-group analyses will be conducted including everyone who received the intervention. Alternatively, if there are significant group differences, separate within-group analyses will be conducted for each condition. Since participants randomised to the two conditions receive the SHAPE intervention at different starting points (i.e. immediately versus post-wait), time will therefore be coded in relation to the start of the intervention rather than time since randomisation for these analyses. Timepoints will therefore include pre-intervention (baseline or post-wait scores), post-intervention (after 8 weeks of intervention), and 6 months post-intervention completion.

For the dichotomous secondary outcome measure, SCID-5 diagnosed PTSD and MDD at 6 months post-intervention completion, a mixed effects logistic regression model will be used. For the between-group analysis, the model will include fixed factors of time (post-intervention, 6-month post-intervention completion), condition (SHAPE, waitlist), and time × condition. Participant will be treated as a random effect. If there is not a significant difference between groups (receiving SHAPE immediately or after waitlist), a within-group analysis will be conducted that will include fixed factors of time (post-intervention, 6-month post-intervention completion), and participant will be treated as a random effect. If there is a significant difference between groups, separate within-group analyses will be conducted for each condition. The stratification variables absence/presence of PTSD based on the SCID-5, depression symptom severity (<15 or 15) based on the PHQ-9, and time since trauma (>/<18 months) based on the PCL-5 will be included as fixed covariates in all models, along with the pre-intervention diagnosis of PTSD and MDD.

For the continuous secondary outcome measures collected at 6 months post-intervention completion, mixed effects regression models will be used. For the between-group analyses (receiving SHAPE immediately or after waitlist), models will include fixed factors of time (post-intervention, 6-month post-intervention completion), condition (SHAPE, waitlist), and time × condition. Participant will be treated as a random effect. If there is not a significant difference between groups, within-group analyses will be conducted that will include fixed factors of time (post-intervention, 6-month post-intervention completion), and participant will be treated as a random effect. If there are significant differences between groups, separate within-group analyses will be conducted for each condition. The stratification variables absence/presence of PTSD based on the SCID-5, depression symptom severity (<15 or 15) based on the PHQ-9, and time since trauma (>/<18 months) based on the PCL-5 will be included as fixed covariates in all models, along with the pre-intervention score of the measure being analysed.

A detailed statistical analysis plan is available to view as a supplementary file.

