#### Main trial analyses

##### Primary outcome

The primary outcome measure will be SCID-5 diagnosed PTSD and MDD at 8 weeks post-random allocation. The primary outcome measure will be analysed using logistic regression. The outcome will be a binary outcome measure whereby, if a participant meets diagnosis for one or both disorders (PTSD and/or MDD), they will score a 1 (present), whereas if a participant does not meet diagnostic criteria for either disorder, they will score a 0 (absent). All participants will begin the trial with a score of 1 since they will have a diagnosis of PTSD and/or MDD at the outset, consistent with eligibility criteria.

Where the primary outcome is measured at one time point, it has been shown that logistic regression is valid with a data missing at random assumption [66]. Complete case analysis will be conducted if missingness is <5%, whereby participants with missing data will be excluded from the primary analysis. Multiple imputation will be conducted as a sensitivity analysis for the primary outcome if missingness is >5% to check for robustness of results.

Models will include fixed factors of condition (SHAPE, waitlist). The stratification variables absence/presence of PTSD assessed with the SCID-5 at baseline, depression symptom severity (<15 or 15) assessed at baseline with the PHQ-9, and time since reported trauma (>/<18 months) assessed at baseline with the PCL-5 will be included as fixed covariates. The significance level will be set to *p* < 0.05 for comparison between the SHAPE and waitlist conditions.

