##### Secondary outcomes

All secondary outcome analyses will be treated as exploratory analyses.

Between-group analyses of the continuous secondary outcome measures will include mixed effects regression models and multiple regression models following the same specifications as the primary outcome measure with additional fixed effects for time, a time by condition interaction, and a random effect for participant for the mixed-effect regression models. Mixed effects regression models allow for the inclusion of all available data from randomised participants (ITT), can account for missing data, and can account for repeated measures [67]. Between-group effect sizes (Cohen’s *d*) will be calculated by dividing the adjusted group difference by the baseline standard deviation.

For secondary outcome measures collected at 4 and 8 weeks post-random allocation (i.e. PCL-5, PHQ-9, GAD-7, PTCI-s, and RIQ-s), statistical models of treatment effects will include categorical fixed factors of time (4 weeks, 8 weeks post-random allocation), condition (SHAPE, waitlist), and the time × condition interaction. The interaction permits the estimation of differences between treatments at each timepoint. Participant will be treated as a random effect to account for between-participant variation.

For secondary outcome measures collected at 8 weeks post-random allocation only (i.e. ISI, ITQ, WEMWBS, CD-RISC, and social support scales), we will fit multiple regression models including condition (SHAPE, waitlist).

The stratification variables absence/presence of PTSD assessed with the SCID-5 at baseline, depression symptom severity (<15 or 15) assessed at baseline with the PHQ-9, and time since reported trauma (>/<18 months) assessed at baseline with the PCL-5 will be included as fixed covariates, along with the baseline score of the measure being analysed. Significance level will be set to *p* < 0.05 for comparison between the SHAPE and waitlist conditions.

To assess for potential correlates of PTSD and MDD symptom change, we will conduct correlational analyses to assess the strength of the relationship between change in posttraumatic cognitions and maladaptive responses to intrusions from baseline to week 4, and from baseline to week 8 and change in PTSD and MDD symptom severity over the same time periods, controlling for baseline scores on these measures. This analysis will be conducted with the whole sample at week 8 to include post-intervention and post-wait participants.

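### At follow-up, a low-powered significance test decides whether the two arms are pooled or split, so non-significance is acted on as if the arms were alike

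*Protocol article*

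**What the plan says.** Under Follow-up analyses, the protocol article first fixes who is analysed: "secondary analyses will be conducted for all participants who received the intervention (i.e. including post-waitlist participants going on to receive SHAPE". A between-group test of immediate against delayed SHAPE then governs the grouping. If it is not significant, "If there are no significant group differences, within-group analyses will be conducted including everyone who received the intervention". The other branch reads: "Alternatively, if there are significant group differences, separate within-group analyses will be conducted for each condition".

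The rule is repeated for the SCID-5 outcome ("If there is not a significant difference between groups (receiving SHAPE immediately or after waitlist), a within-group analysis will be conducted") and again for the continuous measures. The between-group model contains time, condition and their interaction. The pooled within-group model keeps time, the stratification variables and a pre-intervention covariate, with no condition term. For the continuous measures, each model is specific to its outcome, "along with the pre-intervention score of the measure being analysed". This suggests that the choice is made outcome by outcome.

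No equivalence margin, interval criterion or power is stated for this test. The article does not name the deciding term or give a separate significance level. The level stated under Secondary outcomes is: "Significance level will be set to *p* < 0.05 for comparison between the SHAPE and waitlist conditions".

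**The concern.** Pooling without a condition term treats the arms as interchangeable. The only licence for this is a non-significant p-value, from a trial sized for a much larger difference at a different time point. A test with little power will often be non-significant when the arms differ moderately, so the rule cannot separate similar arms from too few data.

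The rule also lets chance choose what is reported. One outcome may have a single estimate across both arms while a related outcome has two arm-specific estimates, with no planned reason for the difference. Stability of effects at 6 months is a stated objective with its own prediction, and these analyses address it.

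**Working it through.** **Inputs from the protocol article (Sample size).** Recovery 50% against 16%, 90% power, alpha 0.05, 39 evaluable per arm (78), 15% attrition, N = 92.

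**Assumptions.** Two-sided 0.05 for the preliminary test. 39 per arm at 6 months, or 33 if a further 15% is lost or does not take up SHAPE (39 × 0.85 = 33.15). Correlation of 0.5 between pre-intervention score and outcome where adjustment is considered.

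**1. Reproducing the plan's figure.** Mean proportion not recovered = (0.50 + 0.84)/2 = 0.67.

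n = [1.96√(2 × 0.67 × 0.33) + 1.2816√(0.25 + 0.1344)]² / 0.34² = (1.303 + 0.795)² / 0.1156 = 38.1, so 39 per arm. 78/0.85 = 91.8, so 92. Both agree with the article. Power at 39 per arm is 90.7%, but for a 34-point difference.

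**2. Power of the preliminary test, continuous outcomes.** Two-sample t-test with non-centrality d√(n₁n₂/(n₁+n₂)). Adjustment divides d by √(1 − 0.5²) = 0.866.

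| Setting | d = 0.3 | d = 0.5 |
|---|---|---|
| 39 vs 33, unadjusted: √17.875 = 4.228, non-centrality 1.27 and 2.11 | 24% | 55% |
| 39 vs 39, adjusted: √19.5 = 4.416, non-centrality 1.53 and 2.55 | 33% | 71% |

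**3. Power, SCID-5 outcome.** For 50% against 65% at 39 per arm: [0.15√39 − 1.96√(2 × 0.575 × 0.425)] / √(0.25 + 0.2275) = (0.937 − 1.370)/0.691 = −0.63, so 27%. At 36 per arm it is 25%. For 50% against 70% at 39 per arm it is 44%, so a true 20-point difference is missed 56% of the time.

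**4. What a non-significant result leaves open.** The 95% interval half-width for the arm difference at 39 per arm is 1.96√(0.5/39) = 0.22 (22 points, rates near 50%), or 1.96√(2/39) = 0.44 SD.

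**5. Pooled and split results in the same trial.** Simulation of 11 equally correlated outcomes, 39 per arm, 20,000 runs. With no true difference, some outcomes are pooled and others split in 22% of trials (correlation 0.7) to 31% (correlation 0.5). With d = 0.3 on every outcome, this happens in 57 to 71%. The count and correlations are assumptions.

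**6. Intervals after the gate.** Simulation of a continuous outcome at post-intervention and 6 months, 39 vs 39 and 39 vs 33, within-person correlation 0.5 or 0.7, true differences 0 to 0.5 SD.
- After a non-significant test, the pooled 95% interval for the average change among recipients covers about 95 to 96%.
- After a significant test with no true difference, arm-specific intervals cover about 67% if time by condition decides. The loss is milder, with coverage near 90%, if the 6-month difference decides. That branch is entered about 5% of the time per outcome.
- By a true difference of 0.5 SD, arm-specific coverage is back to about 95%.

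**The case against.** The stakes are modest. Secondary outcome analyses are labelled exploratory, and the Discussion concedes that 6-month changes cannot be called intervention-specific. The between-arm comparison is run for every outcome before any pooling. Power is not negligible at d = 0.5, particularly with adjustment. The plural wording of the general rule could also mean one overall decision. All of this limits the weight of the point. None of it makes a non-significant test evidence of similarity, and a single overall gate would have the same weakness.

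A reader might infer more than the documents support:
- **That all later intervals are too narrow.** The pooled interval keeps its coverage; only the split branch suffers, and mainly when the true difference is absent or small.
- **That the analysed population changes.** Both branches use every SHAPE recipient; only the grouping changes.
- **That remission during the wait inflates the long-term result.** If all 39 waitlist participants took SHAPE and 16% had already recovered, a crude pooled rate would be (0.5 × 71.76 + 6.24)/78 = 54% rather than 50%. The planned model instead contrasts post-intervention with 6 months. It also adjusts for status at the start of SHAPE ("along with the pre-intervention diagnosis of PTSD and MDD"), which is the post-wait status for the delayed arm.
- **That this covariate breaks the model.** Because "All participants will begin the trial with a score of 1", the composite is constant in a SHAPE-only model, where it simply drops out. With separate indicators for the two disorders, it need not be constant. In a joint model it varies.
- **That there is a 40% chance of at least one spurious split.** 1 − 0.95¹⁰ = 0.40 needs ten independent outcomes; these are related scales.

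**Conclusion.** The point holds for the gate itself. Over 33 to 39 per arm, power is about 24 to 33% at d = 0.3 and 55 to 71% at d = 0.5 (upper values assume adjustment with a correlation of 0.5), and about 27% for 50% against 65% recovery at 39 per arm. Non-significance is compatible with differences of some 20 points or 0.4 SD, so it cannot justify dropping condition. If the rule is applied outcome by outcome, as the measure-specific models suggest, roughly 22 to 31% of trials with no true difference would report a mixture of pooled and split results.

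The effect on interval coverage is confined to arm-specific estimates reported after a significant test. The impact is limited to exploratory follow-up analyses. The 8-week primary result is untouched.

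**What to change.** Remove the significance gate. For each 6-month outcome, fit one model in all who received SHAPE, with time, condition, time by condition, the stratification variables and the pre-intervention covariate. Report the averaged estimate, the arm-specific estimates and the arm difference, each with a 95% confidence interval, whatever the p-value.

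Keep pre-intervention diagnosis in the joint SCID-5 model. Do not restrict the main follow-up analysis to participants with a diagnosis at the start of SHAPE. That would select on a post-randomisation status in the delayed arm and depart from the stated population. It could serve as an optional sensitivity analysis.

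The cost is a change of wording, two more terms than in the pooled model, and slightly wider intervals. No further data are needed.

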### Methods in analysis to handle protocol non-adherence and any statistical methods to handle missing data {27c}

For the primary outcome, if missing data is <5%, this will be handled with complete case analysis whereby participants with missing data at the primary outcome timepoint (8 weeks post-randomisation) will be excluded from the analysis. If missing data is >5%, multiple imputation will be employed.

Due to the secondary analyses being exploratory in nature, no sensitivity analyses will be conducted to test assumptions for missing data. However, the statistical analysis methods used for the secondary measures are able to handle missing data under a data missing at random assumption.

More information on handling protocol non-adherence and missing data is included in the statistical analysis plan [68].

### Methods for additional analyses (e.g. subgroup analyses) {27d}

#### Health economic evaluation

A health economics evaluation will compare the costs involved in administering SHAPE and the costs saved in terms of patient quality of life, working hours, and use of healthcare services. Health economic measures including the iMTA Productivity Cost Questionnaire short (iPCQ) [62], Short Form Health and Labour Questionnaire (SF-HLQ) [65], Client Service Receipt Inventory (CSRI) (*edited*) [61], Quality of Life (EQ-5D-5L) [63], and Recovering Quality of Life (Re-QoL) [64] will be collected at baseline (0 weeks), 8 weeks post-random allocation, and at 6 months post-intervention follow-up. Results will be expressed in costs per group.

#### Qualitative evaluation

Transcripts will be transcribed verbatim, uploaded onto NVivo version 15, and indexed using the framework analysis method [69, 70]. Framework analysis will be used to identify key themes, and findings will be written up alongside the quantitative findings from the RCT [71]. The framework analysis method was chosen since it is a dynamic, grounded, and systematic approach of organising data in a structured way. It allows for between and within case analysis, enabling comparison between, and associations within, cases to be made [72]. We hope this analysis method will allow for our findings to be easily understood by individuals from different disciplinary backgrounds due to its structured and accessible design.

## Methods: monitoring

### Composition of the data monitoring committee, its role and reporting structure {28a}

Not applicable. The TSC will assume the role of the DMC as the trial is deemed to be low risk. There are no stopping rules in place for this trial since it does not use Investigational Medicinal Products (non-CTIMP). Furthermore, there are no foreseen associated risks with completing the questionnaires, assessments, or the intervention.

### Interim analyses {28b}

An interim analysis will be conducted once all available 8-week data have been collected from participants. The results of this interim analysis will not change how the rest of the follow-up is performed, and the trial will not be terminated as it is considered low risk. The results will not be shared with participants, coaches, or assessors until all follow-up data have been collected.

### Frequency and procedures for monitoring trial conduct {29}

The principal investigator will monitor trial conduct and data collection on a weekly basis. Researchers involved in various aspects of the trial will report their progress in various ways. For coaches delivering the intervention, they will complete a coach log after each call outlining what they covered in the call and the time taken for the call and administration. For assessors conducting clinical assessments, they will be required to upload their assessment sheets and a recording of the assessment into a secure shared folder on Nexus 365 OneDrive for Business that only the research team will be able to access. Coaches and assessors will be able to bring any issues or concerns to weekly supervision with a member of the research team.

## Ethics

### Research ethics approval {30}

This study was approved on December 7, 2022, by the Medical Sciences Interdivisional Research Ethics Committee at the University of Oxford, ref R80469/RE008. All participants will give online consent prior to taking part in the trial at two stages, consent to initial assessment and consent to participate in the trial, which will be obtained online by the trial lead. The trial will be conducted in compliance with the principles of the Declaration of Helsinki (1996) and the principles of Good Clinical Practice.

### Plans for communicating important protocol amendments to relevant parties (e.g. trial participants, ethical committees) {31}

Any proposed changes to the protocol will be first discussed within the main research team and TSC. If approved, they will be taken to the ethics committee for final approval. Once approved, these changes will be documented in the pre-registration form online, and study material will be updated. Participants who are signing up for the trial at the time will be informed of these new changes.

### Who will obtain informed consent? {32a}

This randomised controlled trial follows the most up-to-date version of the Declaration of Helsinki. Informed consent will be taken at two time points in the study. The first timepoint is after prospective participants have read the participant information sheet, had sufficient time to consider the study, and ask any questions they may have. The first consent form will be made available remotely to complete online. The second timepoint for taking consent will be after a prospective participant has completed the screening measures and received a structured clinical assessment with a trained assessor. If a participant is eligible to take part in the trial, the lead researcher of the study will send a link to a second online consent form that carefully outlines the participant’s rights and what the study will involve. Both consent forms must be obtained before any intervention is administered to prospective participants.

### Additional consent provisions for collection and use of participant data and biological specimens in ancillary studies, if applicable {32b}

A complementary qualitative interview study will run alongside the trial to assess the suitability, acceptability, and accessibility of the intervention. If a participant or coach is invited to take part in this study, they will be sent an information sheet. If a participant or coach agrees to take part in the study, the lead researcher will invite them to complete a remote consent form before participating in the interview. A copy of the completed consent form will be emailed after they have finished the interview.

We will not be collecting biological specimens in this study.

### Confidentiality {33}

Personal information collected from prospective and enrolled participants will be stored on a secure, two-factor authenticated file only accessible by the main research team. Raw personal data will be kept in this folder for the duration of the trial until all results have been analysed and published, and then personal data will be destroyed. Personal data will be retained beyond this period only if participants provide consent to be contacted for future studies. Participants will be assigned a unique identification number for pseudonymity, and all future data collected will be assigned under their unique ID in separate folders. Participants will not be directly identifiable in any research outputs from this trial unless consent is provided (i.e. consent to provide a testimonial of their experience of the SHAPE intervention).

